### Study hypothesis and objective

This protocol was written in accordance with the Standard Protocol Items: Recommendations for Interventional Trials (SPIRIT) (23). Participants were recruited from the Lung Transplantation Department of the Center of Respiratory Diseases, China-Japan Friendship Hospital, China. The multimodal intensive rehabilitation program is designed to comprehensively improve patients’ respiratory muscle function, voice and swallowing function (24), and limb strength, thereby shortening hospital stay and improving the quality of life. The primary outcome was to analyze the effects of MIRP on the 6 min walking distance in lung transplant recipients. Secondary outcomes were (1) short-term change in health-related quality of life; (2) body skeletal muscle mass and skeletal bone condition; (3) respiratory muscle function and lung function; (4) psycho-emotional states; (5) the state of swallowing function and nutrition; (6) Clinical Frailty Scale; and (7) adverse events related to rehabilitation.

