## Method/design

### Study design

The inclusion criteria are as follows: (1) recipients of unilateral or bilateral lung transplantation and (2) age between 18 and 75 years.

The exclusion criteria are as follows: (1) inability to obtain informed consent from the patient or a legal representative; (2) severe postoperative complications, such as anastomotic leakage, pulmonary embolism, or other major complications requiring prolonged mechanical ventilation or reoperation; (3) dependence on invasive mechanical ventilation or endotracheal intubation when transferred back to the general ward; (4) hemodynamic instability, defined as mean arterial pressure (MAP) < 60 mmHg or > 110 mmHg, heart rate < 50 bpm or > 130 bpm, or the requirement for high-dose vasoactive agents (e.g., norepinephrine > 0.1 μg/kg/min); (5) insufficient respiratory reserve, defined as a ratio of arterial oxygen partial pressure to inspired oxygen fraction (P/F ratio) ≤ 300, or oxygen saturation (SpO₂) ≤ 90% while receiving an inspired oxygen fraction (FiO₂) ≥ 0.6; (6) unstable cardiovascular conditions, including recent myocardial infarction, uncontrolled hypertension, unstable angina, severe arrhythmias, or advanced heart failure; (7) neurological or psychiatric disorders that interfere with rehabilitation participation, such as uncontrolled seizures, severe cognitive impairment, or severe psychiatric illness; and (8) musculoskeletal limitations that preclude active participation in rehabilitation, such as severe arthritis, recent fractures, or recent orthopedic surgery. The withdrawal criteria are as follows: (1) patient or legal representative requests to withdraw consent; (2) development of severe medical complications after enrollment that preclude safe participation in the rehabilitation program; (3) clinical deterioration requiring transfer to the ICU or re-initiation of invasive mechanical ventilation; (4) any adverse events deemed by the treating physician to require discontinuation of the intervention for patient safety; and (5) non-compliance with study procedures that prevents adequate data collection.

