**Figure 2 fig2:**
[figure not shown]
Positioning of a patient during sitting training. The upper left arrow points to a supportive pillow behind the patient’s back, facilitating an upright trunk position. The upper right arrow shows the support under the elbow against the bed rail, which helps stabilize the torso. The overall arrangement allows for the simultaneous use of nasal oxygen/enteral tubes, intravenous access, and monitoring leads without interference.

The supervised intervention concludes at 6 weeks for all participants, at which point they are provided with a standardized, personalized plan for unsupervised rehabilitation. This plan is continued until the 3-month assessment, regardless of whether the patient has been discharged or remains in the hospital.

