### Outcome measurement

The selection of assessment time points was based on clinical relevance and the study objectives. The 6-week assessment was chosen to evaluate the short-term efficacy and immediate impact of MIRP upon completion of the supervised, intensive intervention phase. The 3-month assessment serves as a key mid-term follow-up point to determine the sustainability of initial gains and to capture clinically significant outcomes as patients transition into the maintenance phase of recovery. All outcome assessments will be conducted by trained research assistants who are blinded to the participants’ group allocation. The primary outcome measure of treatment failure is assessed at 3 months after recruitment. The following are assessed at 6 weeks and 3 months after recruitment, including:

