Short-term change in health-related quality of life, based on the modified Barthel Index and 36-Item Short Form Health Survey (SF-36).Body skeletal muscle mass and bone mineral density were assessed using dual-energy X-ray absorptiometry; limb muscle strength was evaluated by measuring isometric knee extension strength using a handheld dynamometer (expressed in kg); limb dimensions were determined by measuring the circumference of the thigh and calf using a non-elastic tape measure; global muscle function was scored using the Medical Research Council (MRC) Scale for muscle strength, which provides a composite score (ranging from 0 to 60) based on the manual testing of six key muscles bilaterally.Respiratory muscle and lung function were comprehensively evaluated using the following objective measures: maximum inspiratory pressure (MIP) to assess inspiratory muscle strength, standard spirometry for lung function parameters, and diaphragmatic ultrasound to quantify diaphragmatic excursion and thickening fraction (TFdi) as key indicators of diaphragmatic performance. Patient-reported dyspnea was assessed using the St. George’s Respiratory Questionnaire (or Dyspnea Rating Scale).Psycho-emotional states, based on the Anxiety Self-Rating Scale and Depression Self-Rating Scale.The state of swallowing function and nutrition, based on the Toronto Dysphagia Bedside Screening Test, 10-item Eating Assessment Tool (EAT-10) Swallowing Screening Scale, grade, roughness, breathiness, asthenia, and strain (GRBAS) grading scale for hoarseness of voice, and the Mann Assessment of Swallowing Ability Scale (MASA).Adverse Events Monitoring: All adverse events (AEs) occurring during or within 24 h of a rehabilitation session were recorded. Examples of monitored AEs included musculoskeletal pain beyond typical soreness, falls, excessive dyspnea, cardiac symptoms, oxygen desaturation >4%, and skin irritation from equipment.

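### The harms outcome is observed only around rehabilitation sessions: delayed harms and harms after sessions stop fall outside it, and capture in weeks 7–13 is undefined

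*Protocol article*

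**What the plan says.** The objectives (Study hypothesis and objective) list, as secondary outcome 7, "adverse events related to rehabilitation". Outcome measurement gives the only recording rule for it: "All adverse events (AEs) occurring during or within" 24 h "of a rehabilitation session were recorded. Examples of monitored AEs included" mainly immediate events: pain beyond ordinary soreness, falls, marked dyspnea, cardiac symptoms, desaturation of more than 4% and skin irritation. Adverse event monitoring belongs to the list introduced by "The following are assessed at 6 weeks and 3 months after recruitment".

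On the timing of sessions, the text after Figure 2 states "The supervised intervention concludes at 6 weeks for all participants". Every participant then receives an unsupervised plan, and "This plan is continued until the 3-month assessment".

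The withdrawal criteria under Study design include "clinical deterioration requiring transfer to the ICU", return to invasive ventilation, severe complications that make participation unsafe, and adverse events that lead the treating physician to stop the intervention.

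**The concern.** A window defined by sessions makes the observation of harm depend on receiving the treatment under test. This has three consequences.

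- **The window closes when a patient does badly.** Once sessions stop because of deterioration or withdrawal, the window ends 24 h after the last session. What follows is outside the outcome as defined. If stopping differs by arm, so does observation.
- **A 24 h limit is a weak stand-in for relatedness.** A harm of rehabilitation that shows itself late, such as a pneumonia, falls outside it.
- **The second half of follow-up has no clear rule.** The schedule assesses adverse events at 3 months, but supervised sessions have ended by then and the status of unsupervised ones is not stated.

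The arms also differ in the number of prescribed sessions, so events noticed because a therapist is present may have more chances of being recorded under MIRP. At stake is whether the trial can compare the safety of an intensive programme with standard care in recent transplant recipients.

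**Working it through.** The article states no figure for this point, so there is none to reproduce. The check counts sessions and then the time that the windows cover.

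**1. Component sessions per week** (from Intervention arm and Control arm)

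| Component | MIRP | Control |
|---|---|---|
| Chest physical therapy | 5 | 5 |
| Inspiratory muscle training | 5 | 5 |
| Cycling, bedridden | 3 | 3 |
| Cycling, seated | 5 | 3 |
| Resistance training | 2 | 1 |
| Swallowing therapy | 3 | 2 |

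Diaphragmatic nerve stimulation has no stated frequency and is not counted separately.

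- MIRP, bedridden: 5 + 5 + 3 + 2 + 3 = 18 a week; × 6 = 108.
- MIRP, seated: 5 + 5 + 5 + 2 + 3 = 20 a week; × 6 = 120.
- Control, either state: 5 + 5 + 3 + 1 + 2 = 16 a week; × 6 = 96.
- Ratio: 18/16 = 1.125 to 20/16 = 1.25, so 13–25% more component sessions under MIRP.

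**2. Share of the week inside a window.** Component counts are not observation time, because 24 h windows overlap. Assume one block of 1 h per treatment day, at a fixed hour, on consecutive days. Each day but the last contributes 24 h and the last contributes 1 + 24 = 25 h.

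- Five days: (4 × 24 + 25)/168 = 121/168 = 72%.
- Six days: (5 × 24 + 25)/168 = 145/168 = 86%.

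Both arms have chest therapy and inspiratory muscle training five times a week. If the other components fall on those days, coverage is about 72% in each arm. The Background gives 5–6 days a week for the intensive programme; if MIRP used a sixth day and control did not, coverage would be 86% against 72%.

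**3. Follow-up after supervised sessions end.** Take 3 months as 13 weeks.

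- Weeks without a supervised session: 13 − 6 = 7; 7/13 = 54%.
- Share of the whole follow-up inside a window, if only supervised sessions count: 6 × 0.720/13 = 33% with five days a week, and 6 × 0.863/13 = 40% with six.

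If unsupervised sessions also open windows, these last figures do not apply. The article gives neither the frequency of those sessions nor how their events would be collected, so no alternative figure can be computed.

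**The case against.** The strongest defence is that the window fits the declared outcome. Secondary outcome 7 concerns events related to rehabilitation, and linking events to sessions is a recognisable way to measure that. Recording all serious events is a wider outcome. This is fair as a reason to keep the rule for minor session-related events. It does not help with related harms that appear late or after sessions have stopped.

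Three stronger readings are tempting, and the document does not support them.

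- **That harms after week 6 are missed.** Adverse events are in the list assessed at 3 months, an unsupervised plan runs until then, and the rule speaks of a rehabilitation session without requiring supervision. Capture is undefined, not excluded.
- **That MIRP patients are observed 25% more, so the comparison is biased.** The 25% is the top of a range and counts components, not time. With sessions five times a week in both arms, calendar coverage may be equal. Higher frequency is also part of the programme, so extra events it causes are partly true harm and not an artefact of recording.
- **That deaths, ICU returns or re-intubations are not recorded at all.** The rule limits one outcome. Several such events are withdrawal criteria, so the trial has to identify them, and a condensed article commonly leaves general serious-event reporting to the full protocol. What can be said is that, beyond 24 h after a session, they lie outside the stated adverse event window.

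**Conclusion.** The point holds in limited form and should be acted on. The article states a rule, and under that rule the harms outcome is observed only around sessions. Delayed harms, and harms after sessions stop through deterioration or withdrawal, fall outside it. This part needs no assumption beyond the text.

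Capture in weeks 7–13 is undefined. The 54% of follow-up without a window, and the overall coverage of 33–40%, hold only if session means supervised session, with 3 months taken as 13 weeks and the daily block assumed above.

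Unequal opportunity between arms is possible but not shown. The 13–25% excess in component sessions matters for events that are noticed because a session is taking place. It implies different observation time only if MIRP uses a sixth day or components are spread over different days.

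**What to change.** Keep the 24 h rule for minor session-related events, and report them both per patient and per session delivered. Both are needed: per-session rates alone would divide away harm that comes from the higher frequency, and per-patient counts alone would hide the difference in opportunity. State whether an unsupervised session opens a window and how its events are collected.

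Add a calendar-time rule: serious adverse events (for example death, ICU transfer, re-intubation, readmission, pneumonia, fall with injury) are recorded in both arms from randomisation to the 3-month visit, regardless of session timing or withdrawal from the intervention, and compared per patient as randomised.

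The cost is one extra CRF page, filled from hospital records and visits already planned, with no change to treatment. Trial status reports recruitment still open in August 2025 and database lock planned for December 2025. For patients already enrolled, some of this would therefore be collected retrospectively, including after discharge.

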### Randomization and allocation concealment

Eligible patients are randomized using an automated system, with randomly permuted blocks, 1:1 to the intervention and standard care groups. This use of an automated randomization system and restricting access to the randomization sequence to only the trial statistician ensures that allocation concealment is maintained.

### Blinding

Due to the pragmatic nature of this trial, participants, care providers, and the research team are not blinded to the allocated treatment. Furthermore, patient representatives advised that participants were highly likely to reveal their treatment allocation to outcome assessors, and therefore, any attempt to blind this group would also be subverted.

### Data collection methods and management

Trial data, including study-specific worksheets and the patient questionnaires, are entered onto a case report form on paper. Data are processed as per the study-specific data management plan. Patient confidentiality is maintained with patients only identified by their assigned unique trial identifier and initials, and all databases are password-protected. Compliance with the protocol and the implemented amendments is carefully reviewed. All protocol amendments to date have received the appropriate regulatory and ethical approvals prior to electronic dissemination to investigators, with appropriate training provided by the China-Japan Hospital Science and Technology Center.

### Dissemination

The study findings will be published in international peer-reviewed journals and presented at both national and international meetings and to appropriate patient groups, with authorship granted to those who have made a substantive intellectual contribution to the study. Requests for data sharing will be reviewed on an individual basis by the chief investigators and the trial management group.

## Discussion

Researchers have described MIRP, an intensive pulmonary rehabilitation (PR) program tailored for pediatric patients after lung transplantation. A case report (25) suggested its potential feasibility and indicated possible improvements in functional exercise capacity, lung function, and quality of life in a 10-year-old recipient. However, as this was a single-case study with inherent limitations such as selection bias and lack of generalizability, further evidence from larger cohort studies or controlled trials is needed to conclusively establish the efficacy and safety of implementing such intensive PR programs in the broader pediatric lung transplant population. Moreover, the mechanisms underlying improvement in exercise capacity with MIRP among patients after LT are not well understood. With regard to the influential factors, peripheral muscle abnormalities have been shown to be the predominant limiting factor to exercise capacity in LT recipients; in addition, the original lung disease and pathophysiology may also influence an individual’s exercise capacity and physical activity (26). Recent studies have shown that exercise contributes to significant improvements in central pulmonary perfusion and peripheral skeletal muscle function that are beneficial for improvement in exercise capacity. This is probably because improved pulmonary perfusion is likely to lead to improved oxygenation and cardiac output and, thus, improvement in exercise tolerance and cardiorespiratory fitness (9). Moreover, Memme et al. (27) reported that exercise could help adjust the volume, structure, and capacity of mitochondria; thus, MIPR may help alleviate the muscle atrophy and damage to the respiratory function of mitochondria resulting from long-term immobilization before and after LT and the use of immunosuppressive drugs.

This study will provide new foundational data to determine whether an integrated model combining chest physical therapy, rehabilitation exercise training, nutrition, and swallowing management can improve physical endurance and quality of life after lung transplantation (24, 28). As intended by Chinese medical organizations, this study has the potential to optimize lung transplantation care in China, and all elements that are positively evaluated in our study have the potential to become part of standard medical care in China. If successful, our plan will expand to other transplanted organs and all regions of China.

## Trial status

Recruitment to the initial pilot study commenced Aug 2022. At the time of the initial journal submission, (Aug 2025), recruitment was ongoing using protocol version 1 (Jul 2022). No safety concerns existed to continue protocol-directed therapy and follow-up of all enrolled patients, with a current plan for database lock in Dec 2025.
